## Abstract

**Background:**

Patients with hypertrophic cardiomyopathy (HCM) are at increased risk of sudden cardiac death (SCD) due to ventricular arrhythmias and other arrhythmias. Screening for arrhythmias is mandatory to assess the individual SCD risk, but long-term electrocardiography (ECG) is rarely performed in routine clinical practice. Intensified monitoring may increase the detection rate of ventricular arrhythmias and identify more patients with an increased SCD risk who are potential candidates for the primary prophylactic implantation of an implantable cardioverter-defibrillator. To date, reliable data on the clinical benefit of prolonged arrhythmia monitoring in patients with HCM are rare.

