### Recruitment

According to the sample size calculation (see Statistical Analysis section), recruiting 34 patients will be sufficient for the statistical analysis. Study participants will receive an echocardiography at rest and during exercise (bicycle ergometry) and a cMRI. In addition, their symptoms, family history, and premedication are collected, and their HCM Risk–SCD calculator score will be calculated. According to this score, patients are allocated to three risk groups: low risk (<4%), intermediate risk (4%-6%), and high risk (>6%) of SCD within 5 years. An ICD is generally recommended in the high-risk group, should be considered in the intermediate-risk group, and is not indicated for the low-risk group [1]. For this study, it is planned to recruit 17 patients with low and 17 with intermediate risk scores. All these patients will receive the 14-day ECG patch.

Patients with HCM between the ages of 18 and 75 years will be included if they have not yet undergone implantable loop recorder, pacemaker, or ICD implantation and if their estimated 5-year SCD risk according to the HCM Risk–SCD calculator score is <6%. A maximum age of 75 years was set as the upper limit, as SCD in patients with HCM mainly occurs at a young age [13]. Patients with a pre-existing cardiac implant (pacemaker, ICD, or implantable loop recorder) or an already accepted indication for it; Morbus Parkinson disease with relevant tremor; a transcoronary ablation of septal hypertrophy procedure in the last 4 weeks; inability to give informed consent; and current symptoms or a history of skin cancer, rash from skin adhesive, or dermatoses (contraindication to wearing the patch) are excluded.

A therapeutic procedure is established for the patient based on the information available to date. Afterward, an ECG patch is applied to the chest to continuously monitor the heart rhythm over 14 days. After completing the 14-day wearing period, patients should return the ECG patch. Any arrhythmias recorded will then be documented, and the therapeutic procedure will be re-evaluated with a recalculation of the HCM Risk–SCD calculator score.

An overview of the study process can be seen in Figure 1.

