### Outcomes

The rate of nsVT detection in the first 24 and 48 hours of monitoring versus the whole 14-day monitoring period will be compared. In addition, the prevalence of AF and other arrhythmias will be examined. Moreover, the results of the cMRI and, if applicable, the results of the genetic examination will be considered. The HCM Risk–SCD calculator score will be recalculated if new findings have occurred.

nsVT is defined as ≥3 consecutive ventricular beats at a rate of 120 beats per minute, lasting for <30 seconds [1]. AF is defined as atrial tachyarrhythmia lasting for >30 seconds [15]. The diagnosis of HCM is based on echocardiography; septum hypertrophy ≥15 mm in the absence of other causes of myocardial hypertrophy or septal or posterior wall thickness ratio >1.3 is required.

At the patients’ request, they will be informed about the rhythm-monitoring results and the resulting therapy changes after the ECG patch has been returned.

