## Results

The primary study objective and primary end point is the prevalence of nsVT in patients with HCM at low to intermediate risk (according to the HCM Risk–SCD calculator) and additional mHealth-based prolonged rhythm monitoring. We will also explore the following secondary end points:

Number of patients undergoing a change in therapeutic procedure (ICD, antiarrhythmic drugs, etc) due to detected nsVT in additional monitoringNumber of patients with detection of AF (duration >30 sec) by prolonged monitoringNumber of patients who experience a change in therapeutic procedure (anticoagulation, antiarrhythmic drugs, catheter ablation, etc) due to detected AFPrevalence of cardiac arrhythmias in patients with positive cMRI findings (>5% late gadolinium enhancement)Prevalence of cardiac arrhythmias in patients with positive genetic diagnosis (detection of HCM-typical gene mutations)

Patient recruitment began in June 2023 and is expected to be completed in February 2024. Data analysis has not yet started. An example table listing patient characteristics and outcomes is provided in Multimedia Appendix 2.

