## Discussion

This prospective study aims to measure the prevalence of nsVT in 34 patients with HCM observed by mHealth-based continuous rhythm monitoring over 14 days compared to standard practice (a 24- and 48-h long-term ECG). Thereby, the frequency of ventricular arrhythmias in the 14 days is compared with the frequency in the first 24 or 48 hours for the same patient (intraindividual comparison). We will evaluate whether the prolonged rhythm monitoring detects nsVT and AF more often compared to conventional 48-hour monitoring and to what extent these findings can induce changes in therapeutic management. It may be speculated that, especially in patients with intermediate HCM Risk–SCD calculator scores, prolonged monitoring may identify patients at high risk, who may potentially benefit from a prophylactic ICD, with higher accuracy. If no rhythm abnormality is detected during the 14-day monitoring, this will not likely occur in everyday life and ICDs can be avoided due to a sufficiently low risk. In addition, a higher diagnostic yield for previously undetected AF may also improve decision-making regarding the need for early anticoagulant therapy.

We set an upper age limit of 75 years because it is known that especially young patients with HCM especially have a higher risk of SCD [13]. Nevertheless, a residual risk remains, so no upper limit for ICDs is defined in the European Society of Cardiology guidelines. Several years ago, the DANISH (The Danish Study to Assess the Efficacy of ICDs in Patients With Nonischemic Systolic Heart Failure on Mortality) study demonstrated no survival benefit from an ICD in patients older than 75 years in a sample of patients with systolic heart failure [18]. We have followed this age limit despite the different patient samples.

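### The therapy-change and re-scoring results have no 24/48-hour benchmark, so they mix changes that a standard-length recording would have prompted with changes that only prolonged monitoring could prompt

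*Protocol article*

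**What the plan says.** The order of events is in Methods, Recruitment. After echocardiography, ergometry, cMRI, history and a baseline score, the plan is set: "A therapeutic procedure is established for the patient based on the information available to date". The patch is then worn for 14 days and returned, and one review follows: "Any arrhythmias recorded will then be documented, and the therapeutic procedure will be re-evaluated with a recalculation of the HCM Risk–SCD calculator score". Methods, Outcomes repeats the re-scoring rule without a time point: "The HCM Risk–SCD calculator score will be recalculated if new findings have occurred".

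The standard-practice benchmark appears for detection: "The rate of nsVT detection in the first 24 and 48 hours of monitoring versus the whole 14-day monitoring period will be compared". The Objective in the Abstract likewise limits the intraindividual comparison to the frequency of ventricular arrhythmias.

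The end points are listed under Results. One counts patients whose therapy changes because of nsVT found in additional monitoring, another those whose therapy changes because of AF. Neither refers to 24 or 48 hours. In the same section the primary end point uses the word for the patch as a whole: "additional mHealth-based prolonged rhythm monitoring".

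The Discussion states the question as whether prolonged monitoring "detects nsVT and AF more often compared to conventional 48-hour monitoring and to what extent these findings can induce changes in therapeutic management".

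**The concern.** The Discussion sets the study's yield, and the management changes that follow from it, against a 48-hour recording. The therapy-change end points measure something else: the difference between the plan made before the patch and the plan made after all 14 days. A patient whose first nsVT falls in hour 10 counts the same as one whose only episode is on day 11, although a 24-hour ECG over the same period would have caught the first.

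The clinical impact named in the study title rests largely on these counts and on the re-scoring. Reported as written, they could be taken as the management effect of extending monitoring to 14 days, while the study would not show how much of that effect a 48-hour recording already delivers.

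**Working it through.** **The plan's own figure.** The sample size compares 25% with 75%, 15 per group. With two-sided α = 0.05 (the article gives no sidedness), power 0.80 and no continuity correction:

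n = [1.96·√(2 × 0.5 × 0.5) + 0.842·√(0.25 × 0.75 + 0.75 × 0.25)]² / 0.50² = (1.386 + 0.515)² / 0.25 = 14.5, so 15 per group and 30 in total. Then 30/0.90 = 33.3, so 34.

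The stated 30 and 34 reproduce, and this point does not touch them.

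**Inputs for the early share**
- Intermediate risk, 14 days: 75% (Introduction; Statistical Analysis).
- Intermediate risk, 48 hours: 34% (Introduction, same cited group).
- First 24 hours, against the same 75%: 16.9% (Discussion).
- Low risk, 14 days: 25% (Statistical Analysis).
- Low risk, 48 hours: not stated. The assumed doubling implies 25%/2 = 12.5%. The cited 24- to 48-hour range is 7% to 42%.

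**Formula.** The first 48 hours are part of the 14 days, so everyone positive at 48 hours is also positive at 14 days. Share already positive = p(48 h) / p(14 d).

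**Results**
1. Intermediate risk at 48 hours: 34/75 = 45%. At 24 hours: 16.9/75 = 23%.
2. Low risk at 48 hours: 12.5/25 = 50%, by the doubling assumption.
3. Both groups, 15 evaluable each. Positive at 14 days: 15 × 0.75 + 15 × 0.25 = 11.25 + 3.75 = 15. Positive by 48 hours: 15 × 0.34 + 15 × 0.125 = 5.1 + 1.875 = 6.975. Share: 6.975/15 = 47%. With 17 per group it is 7.9 of 17, again 47%.
4. Range over the unstated low-risk value, from 7% up to the 14-day ceiling of 25%: (0.34 + 0.07)/(0.75 + 0.25) = 41% to (0.34 + 0.25)/(0.75 + 0.25) = 59%.

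**Effect of nsVT already known at baseline.** Suppose a fraction f of the early positives was known before the patch (not given in the article), and none of the late ones. The early share among new positives is 6.975(1 − f)/(15 − 6.975f): 47% at f = 0, 3.49/11.51 = 30% at f = 0.5, and 0% at f = 1.

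**AF.** The article cites an AF rate for 24 to 48 hours (23%) but none for 14 days, so no early share can be computed for AF-driven changes.

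**The case against.** The strongest reply is that the end points concern new information. The score is recalculated only on new findings, and the nsVT end point refers to additional monitoring, which could mean monitoring beyond what is already at hand. This does not settle the matter. The Results section applies the same adjective to the whole patch recording, the AF end point has no such qualifier, and a finding can be new to the patient's record and still fall in the first 48 hours.

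A second reply concerns the baseline, and here the objection stands. A reader might infer that the baseline plan and score usually rest on no rhythm monitoring, since no long-term ECG is among the listed baseline tests and the Abstract says that "long-term electrocardiography (ECG) is rarely performed in routine clinical practice". The documents do not support that. The remark is about routine practice in general, and its own sentence calls arrhythmia screening mandatory. The calculator asks about nsVT, and the Questionnaires section collects earlier rhythm abnormalities. Some patients will have had prior recordings; how many is not stated.

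Third, the Discussion sentence attaches the 48-hour comparator most directly to detection. It frames the management question but is not an explicit commitment to contrast decisions at 48 hours with decisions at 14 days. That is fair, but it leaves the clinical-impact counts without any benchmark.

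Two further inferences should be avoided. The Discussion's doubt about ICDs concerns all patients with nsVT on prolonged monitoring, not only those with late episodes. And the ratio 8/62 = 13% from the second cited study compares 24 hours with 30 days, so it is not a lower bound for a 14-day window.

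Finally, the recording is continuous, so a breakdown by time remains possible at analysis. That makes the problem easy to repair. It does not change how the end points are defined.

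**Conclusion.** The point holds for the two therapy-change end points and the re-scoring. As defined, they do not separate what the first 48 hours would have prompted from what only longer monitoring could prompt. On the article's rates, about 45% of intermediate-risk nsVT positives and about 47% overall (41% to 59% over the low-risk range) would already be positive at 48 hours; at 24 hours the intermediate-risk share is 23%.

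These figures assume that the cited prevalences apply to this cohort and that no early nsVT was known before the patch; prior knowledge lowers them. A reader might take them as the share of therapy changes misattributed. They are that only if early and late positives are equally likely to have therapy changed. The Discussion reports that patients positive in the first 24 hours have more frequent nsVT and that later ones usually had a single episode, so equality is doubtful.

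The affected end points are secondary and exploratory. The comparison of nsVT detection at 24 and 48 hours with 14 days is sound on this point.

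**What to change.** For every nsVT- or AF-driven therapy change and every score reclassification, record whether the triggering arrhythmia first occurred within 24 hours, within 48 hours or later on the patch. Report the total, and attribute to prolonged monitoring only changes whose trigger first appeared after 48 hours. Recalculate the score from the first 48 hours of findings as a benchmark beside the 14-day score. State in the end-point wording that additional monitoring means the whole patch, or that it means the period after 48 hours. Tabulating which patients had an earlier long-term ECG, and its nsVT result, would show how far the baseline already reflected standard monitoring.

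For patients not yet reviewed, a staged re-evaluation (first 48 hours, then the full recording) is optional. It is more work, since the 48-hour decision is hypothetical and the later findings must be withheld until it is recorded.

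The main change needs no new recordings or patients, only the time of first occurrence and revised wording. It can be applied to patients already reviewed, as 26 of 34 were recruited and no analysis had begun when the article was written. The cost is a smaller number of changes attributed to prolonged monitoring. The rule is also conservative where an early episode was followed by later ones that weighed more in the decision, which is why the total should be shown too.

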**Figure 1 figure1:**
[figure not shown]
Overview of the study process. cMRI: cardiac magnetic resonance imaging; ECG: electrocardiography; EP: endpoint; HCM: hypertrophic obstructive cardiomyopathy; ICD: implantable cardioverter-defibrillator; mHealth: mobile health; nsVT: nonsustained ventricular tachycardia; PM: pacemaker; SCD: sudden cardiac death.

### Questionnaires

At the beginning of study recruitment, various data such as the patient’s family history, previous syncope or rhythm abnormalities will be collected. In addition, secondary causes for left ventricular hypertrophy, such as arterial hypertension, will be queried. At the beginning and after monitoring completion, we will also ask patients if they have any questions, concerns, or requests they want to address with us. After completion of the 14-day monitoring period, the patient’s perception of the mHealth measure will be evaluated through a questionnaire (Multimedia Appendix 1). This questionnaire is based on the System Usability Scale by Brooke [14], a standardized questionnaire for evaluating utensils.

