**Methods:**

Following the sample size calculation, 34 patients with a low or intermediate risk for SCD, assessed by the HCM Risk–SCD calculator, will need to be recruited in this single-center cohort study between June 2023 and February 2024. All patients will receive an ECG patch that records their heart activity over 14 days. In addition, cardiac magnetic resonance imaging and genetic testing data will be integrated into risk stratification. All patients will be asked to complete questionnaires about their symptoms; previous therapy; family history; and, at the end of the study, their experience with the ECG patch-based monitoring.

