## Introduction

Cardiac arrhythmias, especially nonsustained ventricular tachycardia (nsVT) and atrial fibrillation (AF), are important comorbidities of hypertrophic cardiomyopathy (HCM) [1,2]. In particular, nsVT is a predictor of sudden cardiac death (SCD) [3,4]. A well-established risk assessment is the HCM Risk–SCD calculator, which queries, among other parameters, the occurrence of nsVT. It is used for recommendations regarding the primary prophylactic implantation of an implantable cardioverter-defibrillator (ICD) [4].

Therefore, adequate screening for nsVT in patients with HCM is highly relevant. It must be assumed that more intensive monitoring can increase the detection rate of cardiac arrhythmias. For example, in one study, a 14-day long-term Holter electrocardiography (ECG) detected nsVT in up to 75% of intermediate-risk patients with HCM. In the same group, a 48-hour long-term ECG revealed nsVT in only 34% of patients [5,6]. In addition, a trial of 100 patients with HCM in Spain showed a 62% rate of nsVT during 30 days of monitoring compared to 8% in the first 24 hours [7]. In another study, 24- to 48-hour long-term Holter ECGs showed at least one AF episode in 23% of patients with HCM [8]. It can be speculated that prolonged ECG monitoring may increase AF detection, leading to the earlier introduction of oral anticoagulants to prevent embolic complications. Patients with HCM with AF have an exceptionally high risk of embolic complications [1].

The feasibility of mobile health (mHealth)–based screening for arrhythmias has not yet been thoroughly investigated in patients with HCM. Holter long-term ECGs and implantable loop recorders are established in everyday clinical practice. Whereas prolonged Holter monitoring is associated with patient discomfort, implantable devices are expensive, have some limitations concerning specificity in arrhythmia detection [9], and carry a risk of surgical intervention for implantation and explantation. More recently, mHealth ECG recorders have become increasingly available, and thus, it should be investigated to what extent mHealth-based prolonged ECG monitoring is feasible and accepted by patients.

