### Dropout

If the patient wishes to discontinue participation in the study during the 14 days of wearing the device, this is possible at any time and without any disadvantages for the patient. In addition, according to patients’ preferences, they may not be informed about rhythm observations. The study physician should be informed about this and discontinuation. If a patient does not return the patch after the 14 days, this will be counted as a dropout.

In addition, a minimum duration of 288 hours has been established. If the ECG patch is worn for less than this time, exclusion from the study will occur. How long the patch has been worn can easily be determined based on the duration that ECG data is available.

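### The patch-experience questionnaire follows the full 14 days and wear under 288 hours means exclusion from the study, so early removers are likely to be missing from the acceptance result

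*Protocol article*

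**What the plan says.** Four statements in the protocol article bear on this point.

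- **Introduction.** After noting the discomfort of prolonged Holter monitoring and the drawbacks of implanted recorders, the authors conclude that "it should be investigated to what extent mHealth-based prolonged ECG monitoring is feasible and accepted by patients".
- **Abstract, Methods.** "All patients will be asked to complete questionnaires", and the topics include, "at the end of the study, their experience with the ECG patch-based monitoring".
- **Methods, Questionnaires.** "After completion of the 14-day monitoring period, the patient’s perception of the mHealth measure will be evaluated through a questionnaire". This form, based on the System Usability Scale, is the only perception instrument described.
- **Methods, Dropout.** Patients may stop at any time. On wear time, "a minimum duration of 288 hours has been established", and "If the ECG patch is worn for less than this time, exclusion from the study will occur". On the device itself, "If a patient does not return the patch after the 14 days, this will be counted as a dropout".

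Acceptance and usability are not among the primary and secondary end points listed under Results.

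**The concern.** Acceptance is a question about everyone who was fitted with the patch. Someone who takes it off after a few days because it itches or is uncomfortable tells us more about acceptance than someone who wore it to the end. If the form is handed out only once the monitoring period is complete, and those with short wear have by then left the study, the answers come from people already selected for having tolerated the device.

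The missing answers are then likely to be the less favourable ones, and the usability summary would be too high. Analysis cannot repair this, because answers that were never collected cannot be recovered. Recruitment narrows the picture further: people with a history of rash from skin adhesive or of dermatoses are not eligible, so early removal is one of the main remaining signs of poor tolerance.

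**Working it through.** **Step 1. Who is asked, following each section in turn**

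| Patient | Abstract | Questionnaires | Dropout |
|---|---|---|---|
| Wears patch 14 days, returns it | asked | asked | stays in study |
| Removes patch between 288 and 336 hours | asked | unclear | stays in study |
| Removes patch before 288 hours | asked | not asked if the timing is a condition; unclear if it is a date | excluded from study |
| Does not return the patch | asked | unclear | dropout |

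The cut-off is 288/24 = 12 days, or 288/336 = 85.7% of the planned period. The group at issue is therefore those who stop before day 12, not everyone who falls short of 14 days. For this group the Abstract points one way and the Dropout section the other.

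**Step 2. How many patients could be involved**

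Inputs from Statistical Analysis: assumed 14-day prevalences of 25% and 75%, α = 0.05, power 0.8, dropout 10%.

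- The plan's figure reproduces. A two-sided comparison of two proportions without continuity correction needs 15 per group, 30 in total. With dropout, 30/(1 − 0.10) = 33.3, rounded up to 34.
- The plan therefore allows for 0.10 × 34 = 3.4 non-evaluable patients; 34 − 30 = 4 is the whole-number allowance. Hence 3 to 4 of 34.
- This is an upper figure for patients lost through intolerance at the planned dropout. The same 10% has to cover unreturned patches, device failure and withdrawals that have nothing to do with comfort.

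**Step 3. Effect on a mean usability score**

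Let *d* be the share of fitted patients who are not asked and *g* the amount by which their mean score would be lower. Then

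mean in those asked − mean in all fitted = *d* × *g*.

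The documents give no usability scores, so *g* and the 0-100 scoring are assumptions.

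| *d* | *g* = 20 | *g* = 40 |
|---|---|---|
| 10% (planned dropout) | 2 points | 4 points |
| 4/34 = 11.8% | 2.4 points | 4.7 points |
| 20% (twice the plan) | 4 points | 8 points |

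**Step 4. The same for a proportion who accept the patch**

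With *d* = 10% and an assumed 90% acceptance among those asked, the value in all fitted patients is 0.9 × 90% + 0.1 × *b*, where *b* is acceptance among those not asked. For *b* = 0%, 20% and 50% this gives 81%, 83% and 86%, an overstatement of 9, 7 and 4 percentage points. If nobody stops early, the overstatement is zero.

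**The case against.** The strongest reply is that no planned end point is touched. Acceptance is absent from the stated objective, the end points, the statistical analysis section and the conclusions. The sentence in the Introduction is motivation, and the questionnaire is descriptive. This stands, and it limits the point to the acceptance and feasibility message.

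Second, a reader might infer that early removers are never asked. The text does not go that far. The Abstract promises the questionnaire to all patients, the wording under Questionnaires can be read as a date rather than a condition, and no sentence refuses the form to those who stop. What remains is that the Dropout section removes these patients from the study, not merely from the rhythm analysis, so following the rules as written would probably leave them out.

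Third, a reader might infer that completion will be reported as 100%. Nothing says that completion will be calculated among analysed patients only. Unreturned patches are counted as dropouts, and wear time can be read from the recorded ECG. A result such as 31/34 = 91% (exact 95% CI 76% to 98%) is therefore obtainable from what the study already records.

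Fourth, the likely bias is small against sampling error. With 30 respondents and an assumed standard deviation of 15 to 20 points, the 95% half-width is 2.045 × 15/√30 = 5.6 to 2.045 × 20/√30 = 7.5 points, which is more than the 2 to 4 points above. That is fair, although the bias has a predictable direction and the interval would not show it.

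Finally, the questionnaire and the study flow figure are not visible here, and the full protocol may say how forms reach early stoppers. The article nevertheless states both the timing and the exclusion rule, and these two are in tension with its own Abstract.

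**Conclusion.** The point holds as a minor one. As written, the Abstract, Questionnaires and Dropout sections do not agree on whether patients who stop before 288 hours are asked about the patch. The most direct reading of the last two leaves them out. The descriptive usability result is then likely to be biased upward. The primary and listed secondary end points and the sample size are not affected through this route.

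The size rests on assumptions. At the planned dropout at most 3 to 4 of 34 patients are concerned, and a mean score would be about 2 to 4 points too high if they scored 20 to 40 points lower. The direction depends on early removers rating the patch worse, which is plausible where discomfort or a skin reaction was the reason and need not hold where the device failed or was lost. The documents do not support a claim that the study is bound to report good acceptance.

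**What to change.** Reconcile the three sections:

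1. Under Questionnaires, state that the same form is given at patch removal, return or withdrawal, whatever the wear time, with one item on the reason for early removal if the form does not already have one.
2. Under Dropout, state that for this purpose the 288-hour rule governs the rhythm analysis only, and that patients with shorter wear still count for usability and feasibility.
3. Report usability, wear time and the share reaching 288 hours with all patients fitted with a patch as the denominator, and give the number of forms missing.

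This takes a few sentences and at most a handful of extra forms; the sample size and the rhythm analysis stay as they are. There are two costs. Some early removers will not respond, so the bias is reduced rather than removed. And because 26 of the 34 patients were already recruited when the article was written, the change would apply prospectively to only 8; any earlier patient who stopped early would have to be contacted retrospectively.
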